**Figure 2 F2:**
[figure not shown]
**Summary diagram of JIA Foot Care Programme (assessment/intervention/outcome)**.

#### Patient follow up procedures

All participants regardless of allocation will undergo another full assessment once they have proceeded to the end of the trial (12 months from baseline). In the interim period, the primary outcome questionnaire (JAFI) will be posted at 6 months from baseline with a stamped-addressed envelope in order to complete and return to the study personnel. Non-responders will be sent a second questionnaire within 2 weeks, followed by a third a further two weeks later, and then contacted by written letter/telephone. Participants in the intervention arm will receive return appointments every 3 months. Any additional appointments within the intervention arm will be made within the scope of normal clinical practice.

#### Economic evaluation

An economic evaluation aims to assess whether an intervention provides value-for-money relative to its comparator. There are three approaches which can be employed to assess this: cost-effectiveness analysis (CEA), cost utility analysis (CUA) and cost benefit analysis (CBA). This trial provides a unique opportunity to not only assess value-for-money but also consider the issue of outcome measurement in children and adults where parents are used as a proxy respondent, and to further explore the aspects surrounding parental and patient preferences for health care. Therefore, a relatively exhaustive evaluation is proposed which will utilise all three of the economic evaluation approaches.

### Cost effectiveness analysis

As described above, at baseline JAFI will be recorded. Health care resource use will be collected from patient notes and parents/adult suffers will also provide details of other health care use (primary care use), out-of-pocket expenses and productivity loss using a self-completing questionnaire. Health care resource use will be valued using national published costs [45-47] while lost productivity will be valued using the human capital approach.

At 6 and 12 months from baseline outcomes will be reassessed. The difference in outcome between baseline and 6 and 12 months will provide a measure of effectiveness. Costs incurred during the trial will be aggregated to represent an annual cost, and both direct health care costs and indirect/societal costs of the intervention and standard care will be calculated. The economic analysis will compare the costs and outcomes in each arm, and it will estimate the (additional) cost per (additional) unit of improvement of the JAFI, which will be presented in the form of an incremental cost effectiveness ratio (ICER). Confidence limits for the ICER will be estimated using bootstrapping, and the analysis will also produce cost effectiveness acceptability curves (CEACs), which provide a presentation of uncertainty in terms of the threshold of acceptability.

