## Background

Juvenile Idiopathic Arthritis (JIA) is the commonest rheumatic disease in childhood with a variable worldwide prevalence ranging from 0.07 to 4.01 per 1000 children [1], while in the UK the prevalence is estimated at between 0.65 and 2.0 per 1000 children [1-3]. Foot problems have been reported as being common in JIA with 90% of children in a cross-sectional survey presenting with at least one foot problem associated with the disease process [4]. Foot and related problems attributable to JIA include synovitis, deformity, pain, stiffness, limited joint range of motion, enthesitis, and bony erosions [4-8]. As such, many sufferers have a reduced capacity to function [9] poorer health related quality of life (HRQOL) [10,11], and high health care costs have been reported [12,13].

Significant advances in the pharmacological management of JIA have taken place with the advocated earlier use of intra-articular cortico-steroid injections (ICIs), disease modifying anti-rheumatic drugs (DMARDs) and biologic therapies. These drugs have greatly improved the treatment options for paediatric rheumatologists, and functional outcomes appear to have improved as a result [14,15]. This shift towards earlier and more aggressive medical management has not been accompanied by specific foot related research. Further investigation is required to determine the prevalence and severity of foot problems in JIA, and also to evaluate the effectiveness of the current available treatments for such problems in the short and long term.

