### Randomisation

Treatment allocation will be conducted by means of minimisation, a highly effective method of allocation which has been recommended for use in randomised controlled trials [33]. Using this method, treatment allocated to the next trial participant depends on the characteristics of those participants already enrolled, with the ultimate aim of 'minimising' the imbalance between groups [34]. Minimisation in this case will be adopted to achieve balance between groups using the following characteristics:

(i) Age

(ii) Gender

(iii) JAFI-IMP score

This method will be conducted by the same researcher (GH) using the minimisation software package Minim [35].

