### Initial assessments and outcome measures

At baseline all participants will be assessed to ensure they satisfy the inclusion criteria. Demographic and disease characteristic data such as age, gender, height, weight, disease sub-type, date of diagnosis, disease duration will also be recorded. All baseline assessments, primary and secondary outcome measures will be recorded prior to allocation to either the usual care arm or the intervention arm. The medical and physiotherapy care plans will be committed to paper prior to randomisation.

The primary outcome is the Juvenile Arthritis Foot Disability Index (JAFI) [31]. This questionnaire is organised by three dimensions related to impairment (9 items), activity limitation (14 items) and participation restriction (4 items) with a 5-point Likert scale for each item. Each point on the 5-point likert scale represents the frequency of the foot problem stated for that particular item during the past week (0 = Never, 1 = Occasionally/Less than once a week, 2 = Sometimes/Once a week, 3 = Frequently/Two to three times a week, and 4 = Always). Median scores are computed for each dimension. The JAFI is completed by parents of children <10 years and self-completed by adolescent children = 10 years of age. It has been shown to be to be valid and reliable for assessing foot-related impairment and disability among children/adolescents with JIA [31]. The JAFI has not yet been formally validated for use in adult patients with JIA. This questionnaire will be administered at baseline, then 6 (by post) and 12 months from baseline. The exploratory nature of the trial will permit in-depth examination of the suitability of the JAFI as a primary outcome measure for use in definitive multi-centre trials.

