### Sample size

The sample size for the study has been pre-determined by power analysis of the primary outcome measure; the impairment domain of the JAFI questionnaire (JAFI-IMP. Sixty patients (30 in each trial arm) will allow detection of a 1 point reduction in the JAFI-IMP score (a conservative assumption determined by the trial steering committee) at six months from baseline at a significance level of p < 0.05 and power of 90%. These figures take into account the estimated potential participant drop out rate over the first six months of the trial (8 patients in each trial arm). The exploratory nature of the trial will permit in-depth examination of the suitability of the JAFI as a primary outcome measure for use in definitive multi-centre trials.

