### Statistical analysis

The primary analysis will compare the JAFI scores for each dimension between the intervention and control group at six months from baseline. This is to be conducted using a two-sided t-test. Should the distribution of change scores be skewed, a Mann Whitney test may be used to analyse the primary outcome variable in preference to a t-test. The longitudinal JAFI scores, at 0, 6, and 12 months will be analysed using repeated measures ANOVA with post hoc testing to identify significant differences between treatment groups and time points.

Core outcome variables scores for each group will be compared using a confidence interval for the difference in proportions. This will be based on a normal approximation to the binomial distribution.

Changes in predetermined gait variables (see Patients assessments and outcome measures section) from baseline to 12 months from baseline will be investigated within each treatment group using a one-sample procedure (t test or Signed Ranks test) and compared across treatment groups using the equivalent two-sided procedure (t test or Mann-Whitney test).

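### If background drug costs are counted, the unadjusted cost comparison between arms of 30 carries avoidable noise from chance imbalance in biologic use at entry

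*Protocol article*

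**What the plan says.** All references are to the protocol article.

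- **Cost effectiveness analysis.** "Health care resource use will be collected from patient notes", supplemented by a questionnaire on other care, out-of-pocket expenses and lost productivity. Costs are rolled up to an annual figure, and "The economic analysis will compare the costs and outcomes in each arm". The result is an ICER per unit of JAFI, with bootstrap limits and acceptability curves (CEACs). No baseline cost, drug treatment or other covariate is mentioned. One sentence describes the costs as those of the intervention and of standard care, without saying whether systemic drugs belong to them.
- **Cost utility analysis.** This is to be done in a similar way. The cost benefit analysis also needs an incremental cost.
- **Randomisation.** "Minimisation in this case will be adopted to achieve balance between groups using the following characteristics": age, gender and JAFI-IMP. Drug treatment is not on the list.
- **Background.** "disease modifying anti-rheumatic drugs (DMARDs) and biologic therapies" are named as part of current management, and high health care costs are noted.
- **Initial assessments and outcome measures.** "The medical and physiotherapy care plans will be committed to paper prior to randomisation".
- **Sample size.** "Sixty patients (30 in each trial arm) will allow detection of a 1 point reduction in the JAFI-IMP score". No precision target is given for costs.

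**The concern.** Whether a patient is on a biologic at entry is settled before allocation. If biologics are expensive relative to the rest of a patient's yearly care and their cost is counted, a surplus of a few users in one arm moves that arm's mean cost for a reason that has nothing to do with the programme. Nothing in the allocation balances drug treatment directly. Age is a minimisation factor, so some balance may follow if use tracks age, but the article does not rely on that.

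The same cost difference is the numerator of both ICERs and the cost side of the cost benefit analysis. Noise in it widens the bootstrap limits and flattens the CEACs. Much of that noise would be predictable from a variable known before randomisation, so it need not be accepted.

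**Working it through.** **Figures in the plan.** The article gives no figure for costs, so there is none to reproduce. Its only calculation is for JAFI-IMP, with 30 per arm less 8 dropouts leaving 22. For 1 point at 90% power, two-sided 5%, this implies SD = 1/[(1.960 + 1.282) × √(2/22)] = 1.02. The article states no SD, so 60 is attainable but cannot be confirmed. Only the arm size n = 30 is used below.

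**Assumptions, none from the documents.** Share on a biologic at entry p = 0.10, 0.20, 0.30; annual biologic cost C = 5,000 to 10,000 pounds.

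**Step 1: how often the arms differ.** With independent binomial counts, b(x) = P(x users in one arm of 30), and P(|D| ≥ 2) = 1 − Σ b(x)² − 2 Σ b(x)b(x+1).

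| p | P(\|D\| ≥ 2) | P(\|D\| ≥ 3) | P(\|D\| ≥ 4) |
|---|---|---|---|
| 0.10 | 0.51 | 0.27 | 0.13 |
| 0.20 | 0.63 | 0.42 | 0.26 |
| 0.30 | 0.67 | 0.48 | 0.32 |

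If only the 22 completers per arm were costed, P(|D| ≥ 2) would be 0.44, 0.57 and 0.62, but each extra user would weigh 1/22 rather than 1/30.

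**Step 2: what an imbalance does.** An excess of k users shifts the mean cost difference by kC/n.

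- k = 2: 2 × 5,000/30 = 333, to 2 × 10,000/30 = 667 pounds.
- k = 3: 0.10 × C = 500 to 1,000 pounds.

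**Step 3: standard error from entry status alone.** C × √(2p(1−p)/30) = 0.077C, 0.103C and 0.118C for the three shares. The 95% half-width runs from 1.96 × 0.077C ≈ 0.15C to 1.96 × 0.118C ≈ 0.23C.

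**Step 4: gain from adjustment.** Each setting was simulated 4,000 times with 30 per arm, comparing the raw difference with a regression on arm and entry biologic status. Ranges run over p and C.

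| Treatment over the year | SD unadjusted | SD adjusted | Variance removed |
|---|---|---|---|
| No change | 415-1,214 | about 147 | 87-99% |
| 10% of users stop, 5% of others start, part-year cost | 444-1,148 | 264-432 | 65-86% |
| 20% of users stop, 5% of others start, full-year effect | 443-1,176 | 346-763 | 39-58% |

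Other annual costs were assumed to have mean 800 and SD about 570 in rows 1 and 3, and mean 1,000 and SD 800 in row 2. Variance removed is 1 − (adjusted SD/unadjusted SD)² within a setting; for example, row 3 at p = 0.10, C = 5,000 gives 1 − (346/443)² = 0.39. Separate reruns gave 64-87% for row 2 and 37-59% for row 3, hence the rounded range of 35-87% when some patients change treatment.

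Analytic check of row 1 at p = 0.20, C = 5,000: entry status contributes 5,000² × 2 × 0.16/30 = 266,667 and other costs about 2 × 566²/30 = 21,357. The square root of the sum is 537, against a simulated 532. The adjusted value, √21,357 = 146, also agrees.

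**Step 5: consequence for the sign.** This needs a programme cost, taken as 500 pounds per patient (assumed). The unadjusted difference then has the wrong sign in 11-34% of runs in row 1 and 13-33% in row 3. After adjustment this is under 1% and 8-26%.

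**The case against.** The strongest objection is that the article is silent on adjustment rather than opposed to it. A regression within each bootstrap replicate would also fit a sentence about comparing costs by arm, and a cost model's covariates are often left to a fuller plan. This stands in part: a reader might infer that the plan rules out adjustment, and it does not. But the section already fixes cost sources, valuation, aggregation, comparison and uncertainty, and the estimator so described has no covariate. Choosing one after the drug imbalance is known would be open to criticism.

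Second, chance imbalance under randomisation is imprecision, not bias, and the bootstrap limits and CEACs would display it. That is correct. They show the noise but do not remove it.

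Third, background drugs may not be counted at all, since the costs are described as those of the two forms of care. That also stands. If they are excluded the problem disappears, but the section should say so.

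Fourth, a reader might infer that biologic imbalance will swamp the programme's cost, or that the cost difference mainly reflects who was on a biologic. The documents do not support either: they give no drug cost, share of users or programme cost. An excess of three users outweighs the programme only if it costs less than about 0.10C per patient.

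Finally, the gain shrinks when treatment changes during the year, and the article does not say that the care plan records current drugs. Both points hold. Adjustment still reduced the variance in every scenario tried, and the patient notes are a second source for entry status.

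**Conclusion.** The concern holds as a conditional point about precision. The section compares annual costs by arm without restricting them to foot care and without naming an adjustment, and allocation does not balance systemic drug treatment. If background DMARD and biologic costs are counted, avoidable noise enters the cost side of all three economic analyses.

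Under the assumed 10-30% use and 5,000-10,000 pounds a year, an imbalance of two or more users is more likely than not (0.51-0.67). Adjustment for entry status removes roughly 35-87% of the variance when some patients change treatment, and more if none do. The direction of the gain was the same in every scenario; its size depends on assumed costs, shares and treatment stability. No bias in the cost difference is shown, and none is claimed.

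**What to change.** In the cost effectiveness section, state whether background systemic drug costs are part of the annual cost.

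If they are, specify that within each bootstrap replicate the incremental cost comes from a regression of annual cost on arm, biologic/DMARD status at entry and age group. Entry status is read from the care plan written before randomisation or, where that does not record it, from the patient notes at baseline. Use this adjusted difference in the cost effectiveness, cost utility and cost benefit analyses. Show the unadjusted difference and an analysis excluding background drug costs as secondary displays.

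The cost is a few sentences of analysis text, one or two degrees of freedom, and one pre-randomisation variable from records already in use. No extra patients or visits are needed, and patient care does not change.

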### Cost utility analysis

A CUA will be conducted similarly to that described above, whereby the EQ5D will be completed at baseline, and at 6 months and 12 months. The UK tariff [48] will be used to value the health states and QALYs will be estimated using the area under the curve method [49]. An ICER using the cost per QALY gained will be estimated, and in this instance can be more informative than cost per improvement in JAFI, as should the intervention prove to be more effective but also more costly, then it is possible to compare the cost per QALY gained with the National Institute for Health and Clinical Excellence (NICE) threshold.

Notably the EQ5D has only been validated for use in adults, and while there is a child version available, it has not yet been validated. In order to explore the issue of child responses versus parent proxies, given that the target population includes children as well as adults who developed JIA as a child, it is proposed that the children in the study will complete the child version of the EQ5D, while their parents will complete the adult version on behalf of their children. The resulting scores will be compared, and will be used to inform a sensitivity analysis of the CUA to determine whether they influence any decision on value-for-money.

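### The planned bootstrap confidence limits for the ICER have no provision for replicates on both sides of zero effect, and the JAFI effect to be set against the annual cost is not fixed

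*Protocol article*

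**What the plan says.** The Cost effectiveness analysis section of the protocol article defines the ICER as extra cost divided by extra JAFI improvement. On uncertainty it says "Confidence limits for the ICER will be estimated using bootstrapping", and the same sentence adds acceptability curves. On effect it says "The difference in outcome between baseline and 6 and 12 months will provide a measure of effectiveness". On cost it says "Costs incurred during the trial will be aggregated to represent an annual cost".

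The Cost utility analysis section says the work will run along the same lines: "An ICER using the cost per QALY gained will be estimated". QALYs come from the area under the EQ5D curve at 0, 6 and 12 months. If the intervention turns out both better and dearer, the result may be compared with the NICE threshold.

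The only design figures are in the Sample size section: "Sixty patients (30 in each trial arm) will allow detection of a 1 point reduction in the JAFI-IMP score", at six months, with 90% power and a 5% significance level, allowing for 8 dropouts per arm by then. No design figures are given for QALYs, for costs, or for retention between 6 and 12 months.

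**The concern.** A ratio can be ranked from worse to better only while its denominator keeps one sign. If the effect difference changes sign across replicates, two things go wrong.

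- A saving of c with a gain of e gives (−c)/(+e). An extra cost of c with a loss of e gives (+c)/(−e). Both equal −c/e, yet the first means the intervention dominates and the second that it is dominated.
- Replicates with an effect close to zero give ratios that run towards plus or minus infinity.

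Sorting such values and cutting at two points produces finite limits that describe no coherent range of value for money. Cost effectiveness is part of the primary aim stated in the Background, so the interval around the main economic ratio should be readable whatever the trial shows.

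A second, smaller matter is the time horizon. The section names effects at two times and a single annual cost, and does not say which effect is the denominator. If the 6-month effect were used, cost and effect would cover different periods.

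**Working it through.** **Step 1. The plan's own sample size.** No SD is stated, so one has to be assumed. With a two-sided 5% test (the Statistical analysis section says "This is to be conducted using a two-sided t-test") and 90% power, n per arm = 2 × SD² × (1.96 + 1.2816)² / δ². With SD = 1 and δ = 1 this is 2 × 10.51 = 21.0, which the calculation with rounding and margin puts at 22. Then 22 + 8 dropouts = 30 per arm, as stated. Solving back from exactly 22 per arm gives SD 1.02 (normal approximation) or 1.00 (t-test). The plan is therefore consistent with an SD of about 1.

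**Step 2. When the limits fail.** Bootstrap effect differences scatter around the observed difference with roughly its standard error, SE = SD × √(2/n). More than 2.5% of them lie at or below zero when observed difference / SE < 1.96. Over repeated trials with true difference δ:

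P = Φ(1.96 − δ/SE)

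**Step 3. JAFI.** The impairment score is used because it alone has a design effect. Assumed SD 1, 22 per arm: SE = √(2/22) = 0.3015.

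| True difference | δ/SE | P |
|---|---|---|
| 1 point (design effect) | 3.32 | 9% |
| 0.75 point | 2.49 | 30% |
| 0.5 point | 1.66 | 62% |

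A bootstrap simulation (500 trials, 1,000 resamples, 22 per arm, SD 1.023) gave 9% at 1 point, 62% at 0.5 and 86% at 0.25. If retention at 12 months fell to an assumed 18 per arm (SE = √(2/18) = 0.333), the formula gives 15%, 39% and 68% at 1, 0.75 and 0.5 point.

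**Step 4. QALYs.** Every input here is an assumption. The SEs are 0.0387 (SD 0.15, n = 30), 0.0452 (0.15, 22), 0.0516 (0.20, 30) and 0.0603 (0.20, 22).

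| Assumed gain | SD 0.15, n = 30 | SD 0.15, n = 22 | SD 0.20, n = 30 | SD 0.20, n = 22 |
|---|---|---|---|---|
| 0.10 | 27% | 40% | 51% | 62% |
| 0.05 | 75% | 80% | 84% | 87% |
| 0.03 | 88% | 90% | 92% | 93% |

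Best corner: 0.10/0.0387 = 2.58 and Φ(1.96 − 2.58) = 0.27. Worst corner: 0.03/0.0603 = 0.50 and Φ(1.96 − 0.50) = 0.93.

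**Step 5. Horizon.** Let the annual incremental cost be C, spread evenly, and the 6-month effect be E. The time-matched 6-month ratio is (C/2)/E. Dividing the full annual cost by the same effect gives C/E, which is twice as large. This applies only if the 6-month effect is chosen. The QALY measure already spans 12 months and matches an annual cost.

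**The case against.** **The interval type is not stated.** The article names bootstrapping but not the percentile method, and some bootstrap constructions respect the order of the quadrants or allow an unbounded set. A condensed article may leave that choice to a full analysis plan. This stands, and it lowers the severity. It does not remove the point: the text commits to limits on the ratio, and a better summary is available from the same replicates.

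**The acceptability curves already cover the uncertainty.** They do remain valid when the effect crosses zero, so it would be wrong to infer that the economic uncertainty analysis as a whole fails. The confidence limits are promised as well, however, and would be reported beside the curves.

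**The NICE comparison is conditional.** It is raised only for the case of a more effective and more costly intervention. That guards the use of the point estimate; it does not keep the individual replicates in one quadrant. Limits for cost per QALY are also an inference from the statement that the two analyses run alike, since the Cost utility analysis section does not mention limits itself.

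**Crossing zero is not shown to be likely.** A reader might infer that it is likely at this sample size. At the trial's own design effect it is not: about 9% to 10% of trials for the JAFI. It becomes likely only if the true effect is well below 1 point, or for QALYs over much of a range that is wholly assumed.

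**The horizons may already match.** A reader might infer that the annual cost is divided by both the 6- and the 12-month effect, giving two JAFI ratios. The text does not say so. It speaks of one measure of effectiveness, which fits a 12-month difference or a summary over 0, 6 and 12 months equally well. Only the ambiguity stands.

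**Conclusion.** The point holds in limited form. The plan commits to bootstrap limits for a ratio without providing for a denominator that changes sign, and ordinary ordered limits are then uninterpretable. For the JAFI the exposure is small if the design effect is real and substantial if the true effect is about half of it; this rests on an SD of about 1, back-solved from the stated sample size, and on 22 evaluable per arm. The QALY range shows only that the problem could be uncommon or nearly universal, because the documents supply no inputs. The JAFI horizon is unspecified rather than shown to be mismatched. In an exploratory trial, with valid acceptability curves already planned, this is a low-severity improvement to the analysis wording.

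**What to change.** 1. Report the point ICER with the bootstrap scatter on the cost-effectiveness plane.
2. Add a bootstrap confidence interval for incremental net monetary benefit, λ × ΔE − ΔC: at the NICE threshold for QALYs, and over a range of willingness to pay for the JAFI. It is linear in the two mean differences, so it keeps its meaning when ΔE crosses zero.
3. Keep the planned acceptability curves.
4. Quote confidence limits for the ICER only when essentially all replicates have a positive effect difference.
5. State that the annual cost is set against the 12-month JAFI difference, or against the area under the 0, 6 and 12-month JAFI curve. This concerns the JAFI ICER only.

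The cost is a change of wording and a little extra analysis of the same replicates. No additional data or patients are needed.
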